## Abstract

**Purpose:**

Evidence on efficacy and long-term safety of paclitaxel-coated devices is still conflicting. Therefore, this study aims to assess whether sirolimus-coated balloon angioplasty is safe and effective for the treatment of infra-popliteal occlusions in patients with chronic limb-threatening ischemia (CLTI).

**Study design:**

The randomized controlled, single-blinded, multicentre, investigator-initiated study aims to enrol 230 participants with CLTI and infra-popliteal occlusions at up to 25 centres. Patients will be randomized in a 1:1 ratio to either sirolimus-coated balloon angioplasty or to plain old balloon angioplasty (POBA). Bailout stenting in case of flow-limiting dissection or ≥ 50% residual diameter stenosis is permitted.

**Outcome measures:**

Primary outcome is the Kaplan–Meier estimate of primary patency at 6 months, defined as the absence of target lesion occlusion with restoration of in-line flow to the ankle. Key secondary outcome is non-inferiority in the proportionate occurrence of major adverse limb events and perioperative all-cause death at 30 days. Overall, participants will be followed for 36 months to assess further secondary efficacy and safety outcomes.

**Assumed gain of knowledge:**

If sirolimus-coated balloon angioplasty turns out to be superior to uncoated-balloon angioplasty regarding patency of infra-popliteal lesions without safety signals, it could become a welcome treatment option for patients with CLTI.

*Trial Registration* ClinicalTrial.gov Identifier: NCT04772300, German Clinical Trials Register: DRKS00024629.

*Level of Evidence* Level 2a, randomized controlled trial.

## Introduction

Lower-extremity peripheral arterial disease (PAD) affects an estimated 27 million adults in Europe and North America. Main risk factors are smoking, diabetes, dyslipidaemia, and hypertension. The prevalence of PAD rises with age up to 20% among those over 70 years [1]. In advanced PAD, presenting as chronic limb-threatening ischemia (CLTI) the risk of limb loss and cardiovascular death is substantially increased, and thus, current guidelines recommend urgent revascularization [2–4].

Until now, plain old balloon angioplasty (POBA) and provisional bare-metal stenting (BMS) are the standard care for infra-popliteal endovascular revascularization. However, efficacy is not satisfactory. Drug-eluting stents (DESs) have shown to decrease the risk of restenosis in short lesions [5]; however, until now, there is no evidence that this also applies for longer lesions. In addition, permanent implants are associated with potential disadvantages including in-stent restenosis and stent thrombosis. Recent studies found considerable evidence of vessel wall degeneration with paclitaxel-eluting stents [6]. In contrast, angioplasty with drug-coated balloon (DCB) leaves no implant behind and drug release is briefer. However, superiority of paclitaxel-coated balloon angioplasty over POBA is still contradictory [5, 7–14]. Furthermore, long-term safety of paclitaxel-coated devices is still controversial because of the cytotoxic property of paclitaxel and the risk of distal embolization [15–20]. Whether sirolimus, which is characterized by a wider therapeutic range, may serve as a safe and effective alternative to paclitaxel remains to be proven.

The objective of our multicentre, randomized controlled trial is to evaluate whether infra-popliteal angioplasty in patients with CLTI with the commercially marketed MAGIC Touch PTA sirolimus-coated balloon catheter (Concept Medical Inc., Tampa, FL, USA) is superior to POBA regarding efficacy and non-inferior to POBA regarding safety.

## Study Design

The LIMES study (Prospective Multi-Centre Randomized Controlled Trial to Evaluate the Safety and Efficacy of Sirolimus Drug Coated Versus Non-Coated Standard Balloon Angioplasty for the Treatment of Infra-popliteal Occlusions in Patients with Peripheral Arterial Disease) is a prospective, multicentre, single-blinded, investigator-initiated, randomized controlled trial. Up to 25 centres are intended to participate. Eligible patients who provided written informed consent will be allocated at a ratio of 1:1 to either DCB angioplasty with the study device (MAGIC Touch PTA sirolimus-coated balloon catheter) or to POBA with a marketed uncoated balloon catheter (Fig. 1). All study devices have the European certificate of conformity (CE mark). Participants and the independent core laboratory, but not the investigators will be blinded to the treatment allocation. The Friedrich-Schiller-University ethics committee, Jena, Germany approved the study. In addition, written permissions from the respective local ethics committees will be obtained by all participating sites. The study is registered with ClinicalTrials.gov (NCT04772300) and with the German clinical trials register (DRKS00024629). The first patient was enrolled on March 4, 2022.

**Fig. 1 Fig1:**
[figure not shown]
Study flow chart. *Pre-dilation, drug-coated balloon dilation, standard balloon dilation, and post-dilation should last for at least 60 s each. Dilation for 180 s each is strongly recommended. *DCB* drug-coated balloon, *ITT* intention to treat

## Eligibility Criteria

### Inclusion Criteria

Individuals are eligible for trial participation if the following criteria applied.Age ≥ 18 years.Clinical symptoms meet Rutherford category 4 to 6.In case of Rutherford category 5 or 6: individuals with infection grade 0–2 and/or ischemia grade 2–3 according to the Wound, Ischemia, and foot Infection (WIfI) classification.Infra-popliteal lesion above the ankle joint (lesions must not extend above the tibioperoneal trunk or below the tibiotalar joint; treatment must not extend beyond these boundaries for more than 1 cm). A target lesion may extend into the distal popliteal artery segment in case it involves a straight uninterrupted lesion extending from the target vessel. Non-significant stenosis below the ankle joint can be allowed if it is not part of the target lesion and does not require treatment.Participants can only be enrolled once with a single target lesion.Total occlusion (de novo or not stent related reocclusion) of the target vessel as assessed by angiography.The target lesion may consist of multiple stenoses/occlusions of a single target vessel if they are ≤ 5 cm apart and if at least one total occlusion occurs.In case of multiple occluded infrapopliteal arteries, the investigator should assign, at his discretion, that artery as target vessel that is expected to contribute most to the restoration of the in-line flow to the ankle. Non-target vessels can be treated during the same procedure according to the patient’s treatment allocation.Reference vessel diameter (RVD) ≥ 2 mm and ≤ 4 mm by angiographic visual estimatePatency of inflow arteries (< 50% diameter stenosis). Inflow stenosis may be treated during the index procedure to ensure sufficient inflow. Treatment must achieve ≤ 30% residual diameter stenosis. There must be a minimum of 3 cm of healthy vessel between the treated inflow lesion and the target lesion. Use of paclitaxel-coated devices is not permitted.Intraluminal guidewire crossingSuccessful pre-dilation of the target lesion (≤ 50% residual diameter stenosis and no flow-limiting dissection ≥ Grad D according to the National Heart, Lung, and Blood Institute classification)Participant’s declaration of informed consent

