### Exclusion Criteria

Individuals are excluded from trial participation if any of the following criteria applied.Stroke or heart attack less than 30 days prior to enrolment.History of or planned target limb amputation above the metatarsal level.Neurotrophic ulcers, heel pressure ulcers, or calcaneal ulcers with risk of major amputation.Any vascular surgical procedure or intervention performed in the target limb within 30 days prior to or planned within 30-day post-index procedure.Stent implantation or bypass surgery in the target vessel prior to randomization (if a stent is already present in the target vessel, there must be a distance of at least 3 cm to the target lesion).Vascular treatment with drug-coated balloons within 6 months prior to index procedure.Known or suspected active infection other than associated with target limb wounds.Infection grade 3 and ischemia grade 0 and/or 1 according to WIfI classification.Active osteomyelitis beyond cortical involvement of the bone (excluding phalanges).Vasculitis, systemic lupus erythematosus, or polymyalgia rheumatica on active treatment.Presence of fresh thrombus in the target lesion.Presence of aneurysm in the target vessel.Systemic corticosteroid therapy (expected dosage > 5 mg of prednisolone or equivalent per day within 9 months after the index procedure).Known allergies or sensitivity to heparin, aspirin, other anticoagulant/antiplatelet therapies, sirolimus, paclitaxel, or contrast media that cannot be adequately pre-treated prior to index procedure.Target lesion requires treatment with alternative therapies such as primary stenting, laser, lithotripsy, thrombectomy, atherectomy, brachytherapy, re-entry devices (intra-arterial lysis ≥ 4 weeks before the index procedure is permitted).Significant gastrointestinal bleeding or any coagulopathy that would contraindicate anti-platelet therapy.Pregnant or lactating womenLife expectancy of less than one year in the opinion of the investigator.Participant is enrolled in another investigational drug-, device-, or biologic study.

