## Intervention

After intraluminal guide wire crossing, pre-dilation of the target lesion with a standard balloon catheter for at least 60 s (180 s strongly recommended) is mandatory in all participants. Nominal diameter should match the distal reference vessel diameter. Immediately after successful pre-dilation, participants will be randomly allocated to either angioplasty with sirolimus-coated balloon (s) (intervention group) or angioplasty with uncoated standard balloon (s) (control group). Participants but not investigators will be blinded to the allocation. Prior to the study intervention, inflow-stenosis ≥ 50% must be treated to achieve ≤ 30% diameter stenosis.

Balloon dilation for angioplasty of the target lesion with either DCB or POBA should be maintained for at least 60 s. Maximum inflation time as per institution’s standard of care is recommended. Nominal balloon diameter should match the distal reference vessel diameter. Balloon length should exceed the target lesion by at least 5 mm proximal and 5 mm distal. If more than one balloon is necessary for complete lesion coverage, multiple balloons should overlap by at least 5 mm. In participants with ≥ 50% residual diameter stenosis or flow-limiting dissection, a prolonged post-dilation of at least 60 s (180 s strongly recommended) must be performed. In case of < 50% residual diameter stenosis, post-dilation is left to the investigator’s discretion. If post-dilation remains unsuccessful (residual diameter stenosis ≥ 50% or flow-limiting dissection), bailout stenting with self-expanding bare nitinol stent (s) is permitted (Fig. 1).

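### The inflow rule bars paclitaxel-coated devices only, so the drug under test may be used on inflow lesions before allocation, including in later controls; a one-line widening removes a small possible dilution

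*Protocol article*

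**What the plan says.** All references are to the protocol article.

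- **Inclusion Criteria, inflow item.** Inflow arteries must be patent. "Inflow stenosis may be treated during the index procedure to ensure sufficient inflow", with at least 3 cm of healthy vessel before the target lesion. The only drug-related limit on the device is "between the treated inflow lesion and the target lesion. Use of paclitaxel-coated devices is not permitted".
- **Inclusion Criteria, item on several occluded infrapopliteal arteries.** "Non-target vessels can be treated during the same procedure according to the patient’s treatment allocation".
- **Exclusion Criteria.** One criterion reads "Vascular treatment with drug-coated balloons within 6 months prior to index procedure". It names no drug, so it covers any coating, but it stops at the index procedure.
- **Intervention.** "Immediately after successful pre-dilation, participants will be randomly allocated". On inflow: "Prior to the study intervention, inflow-stenosis ≥ 50% must be treated to achieve ≤ 30% diameter stenosis". For a failed result at the target lesion, "bailout stenting with self-expanding bare nitinol stent (s) is permitted".
- **Introduction and Study Design.** The study balloon carries sirolimus and is a marketed, CE-marked product. The comparator is an uncoated balloon.

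**The concern.** The sponsor saw that a drug-coated device on the inflow vessel could disturb the trial and wrote a rule against it. That rule names paclitaxel, while the drug that separates the two arms is sirolimus. A participant who had a sirolimus balloon anywhere in the vasculature a month earlier is excluded. A participant who has one placed upstream in the target limb minutes before allocation is not.

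If such a participant is assigned to control, the control limb contains the drug under test. At stake is a blurred contrast between the arms. For patency, blurring lowers the chance of showing a real benefit. For the key safety outcome it works the other way: if sirolimus did raise 30-day MALE-POD, exposed controls would share some of the excess, and non-inferiority would be slightly easier to declare.

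**Working it through.** **1. Does another rule close the gap?** None in the article does.

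| Rule | Reaches a sirolimus inflow device used before allocation? |
|---|---|
| Inflow item, Inclusion Criteria | No; names paclitaxel only |
| Drug-coated balloon exclusion, Exclusion Criteria | No; earlier treatment only |
| Non-target vessels follow the allocation, Inclusion Criteria | No; no allocation exists yet |
| Bare stents, Intervention | No; bailout at the target lesion only |

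**2. The plan's own sample size.** Inputs from Statistics: control patency 55%, difference 20 points (so 75%), 80% power, two-sided 5%, 20% drop-out.

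- Hazard ratio = ln(0.75)/ln(0.55) = 0.481.
- Freedman events = [(1 + 0.481)/(1 − 0.481)]² × (1.960 + 0.842)² = 64.
- Mean event probability = (0.45 + 0.25)/2 = 0.35, and 64/0.35 = 182.9, so 92 per arm (184 in total).
- 184/0.8 = 230, the stated figure.

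**3. Dilution of the primary comparison.** Let c be the share of controls with a sirolimus inflow device, and f the share of the 20-point benefit that such a device carries to the target lesion. The document gives neither, so both are assumptions. The sirolimus arm is held at 75%, meaning that an inflow device adds nothing to a coated target-lesion balloon.

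Control patency = 0.55 + 0.20·c·f. Power is taken from the two-proportion normal approximation with 92 per arm:

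Φ{[Δ − 1.96·√(2·p̄(1−p̄)/92)] / √[(p₁(1−p₁) + p₂(1−p₂))/92]}

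Here p₁ and p₂ are the patency rates of the two arms, Δ is their difference and p̄ their mean.

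- Undiluted: Δ = 0.20, null standard error 0.0703, alternative standard error 0.0688. (0.20 − 0.1378)/0.0688 = 0.904, so power is 81.7%.
- c = 20%, f = 0.25: control patency 0.56, Δ = 0.19. (0.19 − 0.1374)/0.0687 = 0.766, so power is 77.8%.

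| Controls exposed (c) | f = 0 | f = 0.10 | f = 0.25 |
|---|---|---|---|
| 5% | 81.7% | 81.3% | 80.8% |
| 10% | 81.7% | 81.0% | 79.8% |
| 20% | 81.7% | 80.2% | 77.8% |

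**4. Effect on the key safety test.** Inputs from Statistics: Farrington–Manning test, margin 10 points, one-sided 2.5%, 115 per arm. The chance of declaring non-inferiority was obtained by exact enumeration of both binomial distributions.

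- Planned case, 1% risk in both arms: non-inferiority is declared 99.9% of the time. With no excess to dilute, the issue does not arise.
- Assumed true excess at the margin, 11% against 1%: non-inferiority is wrongly declared 1.8% of the time without dilution. With control risk 0.01 + 0.10·c·f and f = 0.25, this becomes 2.0%, 2.3% and 2.7% for c = 5%, 10% and 20%. With f = 0.10 it is 2.0% and 2.2% for c = 10% and 20%.
- If the inflow risk adds in both arms alike, f = 0.25 gives at most 1.9% at c = 20%.

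**The case against.** **The size rests on assumptions.** The article gives no rate of sirolimus inflow use and no carry-over. Patency is judged at the target lesion, at least 3 cm of healthy vessel away, so carry-over may be nil, and power is then unchanged. The safety figures also need a true excess near 10 points, where the plan expects about 1% in both arms. In addition, an intervention counts toward MALE-POD only if it involves infra-popliteal arteries, although amputation and death count in any case. All of this stands, and it is why the point is minor.

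**Naming paclitaxel has a reason.** The Introduction and Discussion describe its long-term safety as unsettled, so barring it from the limb makes sense. This also stands: the rule contradicts nothing. It simply stops short of the drug being tested.

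**The non-target-vessel rule might cover inflow arteries.** Its place in the item on infrapopliteal occlusions suggests that it does not. Even on the wider reading, it cannot govern treatment given before the allocation is known.

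**The article condenses a fuller protocol**, which may state a wider rule. That is possible. The point concerns the rule as printed here, which is stated and drawn too narrowly.

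**A stronger reading is tempting.** The inflow sentence in Intervention says only that treatment comes before the study intervention, and it follows the sentences on allocation and on blinding ("Participants but not investigators will be blinded to the allocation"). A reader might infer that operators who know the arm could choose the inflow device accordingly, which would be bias and not dilution. The document does not support this. Inflow patency is an entry criterion, Study Design says that eligible patients are allocated, and Table 1 places the study angioplasty directly after allocation with no step between. The order of sentences in one paragraph is too little to set against that.

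**Conclusion.** The gap is real in the article's text, and its consequence is limited. A sirolimus-coated device may be used on an inflow lesion of the target limb before allocation, including in participants later assigned to control. Such use is balanced by randomization and does not bias the comparison. It can only dilute it, against the trial's aim for patency and slightly in its favour for 30-day MALE-POD.

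Under the assumed ranges (5% to 20% of controls exposed, zero to one-quarter carry-over), the loss of power is between 0 and about 4 points (81.7% − 77.8% = 3.9). On safety, the error rate at the margin passes the nominal 2.5% only near the top of those ranges, and only if the inflow risk does not add in the sirolimus arm. Larger losses would require an upstream balloon to act almost like one at the target lesion, which nothing in the document suggests. This is an inexpensive improvement that the sponsor could make; it is not a flaw that threatens the trial's conclusions.

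**What to change.** In the inflow item of the Inclusion Criteria, replace the sentence on paclitaxel-coated devices with: *Use of any drug-coated or drug-eluting device for inflow treatment is not permitted, in either arm.* This matches the any-drug scope of the 6-month exclusion. Sample size, outcomes and tests stay as they are, and the planned contrast of 75% against 55% is kept free of this source of dilution. No change to the Intervention section is needed.

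Enrolment began in March 2022, so the new wording reaches only later participants. For those already enrolled, an optional sensitivity analysis of the primary and key safety outcomes can leave out anyone who had a drug-coated inflow device before allocation. Because it selects on a feature fixed before randomization, it keeps the randomized comparison intact.

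The cost is one amended sentence and slightly less device choice for inflow lesions. Little choice is lost, since paclitaxel is already barred there.

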### Exclusion Criteria

Individuals are excluded from trial participation if any of the following criteria applied.Stroke or heart attack less than 30 days prior to enrolment.History of or planned target limb amputation above the metatarsal level.Neurotrophic ulcers, heel pressure ulcers, or calcaneal ulcers with risk of major amputation.Any vascular surgical procedure or intervention performed in the target limb within 30 days prior to or planned within 30-day post-index procedure.Stent implantation or bypass surgery in the target vessel prior to randomization (if a stent is already present in the target vessel, there must be a distance of at least 3 cm to the target lesion).Vascular treatment with drug-coated balloons within 6 months prior to index procedure.Known or suspected active infection other than associated with target limb wounds.Infection grade 3 and ischemia grade 0 and/or 1 according to WIfI classification.Active osteomyelitis beyond cortical involvement of the bone (excluding phalanges).Vasculitis, systemic lupus erythematosus, or polymyalgia rheumatica on active treatment.Presence of fresh thrombus in the target lesion.Presence of aneurysm in the target vessel.Systemic corticosteroid therapy (expected dosage > 5 mg of prednisolone or equivalent per day within 9 months after the index procedure).Known allergies or sensitivity to heparin, aspirin, other anticoagulant/antiplatelet therapies, sirolimus, paclitaxel, or contrast media that cannot be adequately pre-treated prior to index procedure.Target lesion requires treatment with alternative therapies such as primary stenting, laser, lithotripsy, thrombectomy, atherectomy, brachytherapy, re-entry devices (intra-arterial lysis ≥ 4 weeks before the index procedure is permitted).Significant gastrointestinal bleeding or any coagulopathy that would contraindicate anti-platelet therapy.Pregnant or lactating womenLife expectancy of less than one year in the opinion of the investigator.Participant is enrolled in another investigational drug-, device-, or biologic study.

## Intervention

After intraluminal guide wire crossing, pre-dilation of the target lesion with a standard balloon catheter for at least 60 s (180 s strongly recommended) is mandatory in all participants. Nominal diameter should match the distal reference vessel diameter. Immediately after successful pre-dilation, participants will be randomly allocated to either angioplasty with sirolimus-coated balloon (s) (intervention group) or angioplasty with uncoated standard balloon (s) (control group). Participants but not investigators will be blinded to the allocation. Prior to the study intervention, inflow-stenosis ≥ 50% must be treated to achieve ≤ 30% diameter stenosis.

Balloon dilation for angioplasty of the target lesion with either DCB or POBA should be maintained for at least 60 s. Maximum inflation time as per institution’s standard of care is recommended. Nominal balloon diameter should match the distal reference vessel diameter. Balloon length should exceed the target lesion by at least 5 mm proximal and 5 mm distal. If more than one balloon is necessary for complete lesion coverage, multiple balloons should overlap by at least 5 mm. In participants with ≥ 50% residual diameter stenosis or flow-limiting dissection, a prolonged post-dilation of at least 60 s (180 s strongly recommended) must be performed. In case of < 50% residual diameter stenosis, post-dilation is left to the investigator’s discretion. If post-dilation remains unsuccessful (residual diameter stenosis ≥ 50% or flow-limiting dissection), bailout stenting with self-expanding bare nitinol stent (s) is permitted (Fig. 1).

### Concomitant Medication

Antiplatelet therapy should be used in both study arms according to clinical routine and under consideration of concomitant diseases. Prior to the index procedure, it is strongly recommended to administer dual antiplatelet therapy (DAPT) as a combination of aspirin (100 mg daily at least 3 days before the procedure or a loading dose of 500 mg) and clopidogrel (75 mg daily at least 3 days before the procedure or a loading dose of 300 mg), or aspirin and rivaroxaban (2.5 mg twice a day) per hospital standard of care. During the index procedure, participants must receive appropriate anticoagulation by means of heparin according to the institution’s standard of care. DAPT is recommended for at least 4 weeks after index procedure (aspirin 100 mg daily, clopidogrel 75 mg daily) and single antiplatelet therapy indefinitely thereafter (aspirin 100 mg daily) according to centres’ standard of care.

